#### **4.6 Withdrawal criteria**

Subjects can discontinue their participation in the study at any time without any consequence to his/her continued treatment. The investigator/sponsor can at any time terminate the study for a subject due to, e.g., unacceptable adverse events/adverse reactions or because the subject does not follow procedures in the study protocol. If the subject discontinues the study, follow-up of this subject will be performed according to the clinic's routine.

## 4.7 End of study

The study will end when all patients enrolled in trial have been followed for 5 years, died, withdrawn consent or are lost to follow-up. The trial steering committee may end enrolment at any time if it is deemed that this is in the best interest of the patients. The study may be prematurely terminated due to a high number of serious adverse events related to the IMP or if the enrollment process cannot be completed within a reasonable time frame.

The end of the study will be reported to the MPA within 90 days, or 15 days if the study is terminated prematurely. The Investigators will inform participants and ensure that the appropriate follow up is arranged for all involved.

# 5 Study treatment

## 5.1 Intervention

**Group IPLA:** Ropivacaine 0.2%. After opening the peritoneal cavity and before any surgical dissection, 40 ml of the Ropivacaine will be rinsed in all quadrants within the abdominal cavity under direct vision after opening the peritoneum in order to achieve uniform spread. This will be repeated on two further occasions, first half way through the surgical procedure as estimated by the surgeon and again before closing the abdominal cavity. After the procedure is completed, a plastic multi-port catheter will be inserted lateral to the surgical incision and placed in a way that the tip of the catheter is in the pelvic cavity and the opposite end brought out through the abdominal wall, lateral to the skin incision and fixed with dressing. Ten ml of the Ropivacaine 0.2% will be injected intermittently every other hour via an infusion pump (CADD-Solis) via a bacterial filter that will be programmed to administer an intraperitoneal infusion of 10 mL Ropivacaine 2mg/ml as a bolus injection every other hour for 72 h postoperatively. 72 hours after the end of the surgical procedure the intermittent infusion ends and the intraperitoneal catheter is removed. The amount of infused Ropivacaine 2mg/ml by intraperitoneal infusion will be recorded and the infusion bags discarded in a secure fashion.

## 5.2 Control

**Group Control:** 0.9% saline will be used instead of Ropivacaine in an identical manner described above.

## 5.3 Drug preparation

A nurse who is not involved in patient care will prepare the test medications.

During Surgery: Three sterile 50 ml syringes will be given to the operating nurse prior to surgery start. These will contain 40 ml of either Ropivacaine 2 mg/ml or 0.9% saline: Dose 1, 2 or 3, to be administered at the time of opening the peritoneum, in the middle of surgery and before closing the peritoneum respectively as explained below.

Ropivacaine 0.2% or 0.9% saline will be used as intervention. Three syringes will be given to the operating nurse prior to surgery start. These will contain 40 ml each of Ropivacaine 2 mg/ml) or 0.9% saline (depending on randomization group). After opening the peritoneal cavity and before any surgical dissection, 40 ml of the Ropivacaine or 0.9% saline will be injected in different quadrants within the abdominal cavity under direct vision in order to achieve uniform spread within the abdomen (Dose 1), and the same volume will be injected intraperitoneally to cover the surface of the cavity on two further occasions, first half way through the surgical procedure as estimated by the surgeon (Dose 2) and again before closing the peritoneal cavity (Dose 3). At the end of the procedure, a plastic multi-port catheter will be inserted lateral to the surgical incision and placed in a way that the tip of the catheter is in the pelvic cavity and the opposite end brought out through the abdominal wall, lateral to the skin incision and fixed with dressing.

Post-operative management: All women will be managed in a high-dependency post-operative care unit overnight as appropriate. An epidural infusion containing Ropivacaine 2 mg/ml and Sufentanil 1µg/ml will be administered continuously as per hospital routine (usually 4-14 ml/hour for 3 to 5 days after surgery) for pain management. In case of pain not relieved by epidural analgesia, nurse-controlled intravenous morphine or morphine equivalent as per hospital routine (usually 1-2 mg). Additionally, ten ml of the Ropivacaine 0.2% or 0.9% saline (depending on group allotment) will be injected intermittently every other hour through a bacterial filter and via an infusion pump (CADD-Solis) for 72 h postoperatively. The patients will be transferred to the general ward or later rehabilitation until ready for home discharge, which usually occurs on postoperative day 6 - 14, according to hospital routines. Patients will be followed-up via the hospital journal for later assessment of death at 3- or 5 years after surgery according to existing hospital routines.

## **6 Routine anesthesia and surgery**

Anesthesia: All patients will be given premedication and intraoperative anesthesia according to standardized protocol at all the participating hospitals. A thoracic epidural will be inserted usually at the Th9-Th11 level before induction of general anesthesia. Usually, during surgery, 0.5% Ropivacaine 3-5 mL/hours will be used for pain management. Intravenous injection of Propofol and Remifentanil or equivalent will be used for induction of anesthesia Maintenance of anesthesia is a combination of epidural and inhalation anesthesia during the surgical

procedure and supplemented with infusion of Remifentanyl or equivalent if needed. To achieve neuromuscular blockade Rocuronium or equivalent will be used and will be monitored with train of four. Mechanical ventilation with oxygen in air will be used. Monitoring will include: arterial radial line, oxygen saturation and ECG monitoring. If needed, goal-directed therapy and invasive monitoring guidance will be used to standardize intraoperative fluid management. Mean arterial pressure will be maintained above 65mmHg. Cardiac index >2.5 or stroke volume variation <15% will be the cut-off for hemodynamic instability and will be treated with fluid substitution. Hypotension will be treated with norepinephrine infusion if needed.

Surgery: Will be performed by as per clinical routine. The study treatment will not interfere with any part of the surgical treatment. If per-operative evaluation excludes the patients from cytoreductive surgery because disease extent and the abdomen is closed without any resection of tumor, the participant is excluded from the IPLA-OVCA trial.

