#### **4.5 Blinding and code-breaking**

After allocation has been established, the unblinded nurse then prepares, verifies and label the study drugs in a confined room where both Ropivacaine and Placebo are stored. The syringes and bags for infusion are marked with the patient's unique study number generated at time of randomization. After the intervention/placebo has been prepared their original containers must be put in plastic bag without transparency, closed and then discarded. Both intervention and placebo are color and odorless transparent fluids why blinding can be maintained. The bag for intermittent infusion during the following 72 hours after end of the surgical procedure is covered/masked and secured from opening also marked with patient's study number.

The code list for which treatment the patient was allocated to will be retained in a locked area/cupboard by the unblinded study nurses, not accessible by participating observers or other personnel in the operating rooms, wards or by the attending surgeon, anesthesiologist or oncologist. In this way, full blinding will be achieved at all stages until the end of the study (last patient recruited and followed-up until initiation of adjuvant chemotherapy).

Code-breaking is permitted only if there is a serious negative reaction of IMP to the patient and when determination of the IMP is essential for further management of the patient. The principal investigator should be contacted for code breaking. The contact information to the PI is included in the medical records for each randomized patient. The coordinating investigator will maintain a log of all code-breakings that occur during the trial. The reason for breaking the code must be specified.

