### 16.2 Post-operative morbidity score (POMS)

Post-operative morbidity according to the post-operative morbidity score (45)

| Morbidity type | Criteria                                                                                                                 | Source of data      |
|----------------|--------------------------------------------------------------------------------------------------------------------------|---------------------|
| Pulmonary      | Has the patient developed a new requirement for oxygen or respiratory support?                                           | Patient observation |
|                |                                                                                                                          | Treatment chart     |
| Infectious     | Currently on antibiotics and/or has had a temperature of >38°C in the last 24 hr.                                        | Treatment chart     |
|                |                                                                                                                          | Observation chart   |
| Renal          | Presence of oliguria <500 mL/24 hr; increased serum creatinine (>30% from preoperative level); urinary catheter in situ. | Fluid balance chart |
|                |                                                                                                                          | Biochemistry result |
|                |                                                                                                                          | Patient observation |

| Morbidity type   | Criteria                                                                                                                                                                                                                                                                                                       | Source of data      |
|------------------|----------------------------------------------------------------------------------------------------------------------------------------------------------------------------------------------------------------------------------------------------------------------------------------------------------------|---------------------|

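### Section 6 states the intraoperative fluid trigger backwards: the cardiac index and stroke volume variation values called unstable are the acceptable ones

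*Protocol*

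**What the plan says.** Section 6 of the protocol describes anesthesia that is meant to be uniform across sites: "All patients will be given premedication and intraoperative anesthesia according to standardized protocol at all the participating hospitals". On fluid, it begins with "If needed, goal-directed therapy and invasive monitoring guidance will be used to standardize intraoperative fluid management", and then sets a pressure goal: "Mean arterial pressure will be maintained above 65mmHg". The sentence at issue comes next: "Cardiac index >2.5 or stroke volume variation <15% will be the cut-off for hemodynamic instability and will be treated with fluid substitution". Low pressure has a separate rule: "Hypotension will be treated with norepinephrine infusion if needed".

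The cardiac index and stroke volume variation rule appears nowhere else in the protocol, so no other section confirms or corrects it.

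**The concern.** The sentence does three things: it names a state (instability), gives the values that define it, and attaches an action (fluid). The values are on the wrong side for that state. Cardiac index is cardiac output scaled to body size, so values above the limit are the adequate ones. Stroke volume variation rises when the circulation is short of volume, so values below the limit speak against giving fluid. This is general physiology and does not rest on any cited source.

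At stake is a treatment threshold in operative text that is meant to standardize care. Followed to the letter, it would give fluid to women who do not need it and leave out those who most clearly do. This is an error of wording and does not challenge the trial design.

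**Working it through.** No power, event or alpha figure is involved, and the plan gives no figure to reproduce. The check is one of direction, followed by one of logic.

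**Direction within the document.** The pressure sentence just before uses its limit to mark the side to be kept (above 65 mmHg). The disputed sentence uses limits of the same kind but calls those ranges the ones to be treated. Where the protocol defines an abnormal state, as in the renal row of the morbidity table in section 16.2, the signs point to the abnormal side: "Presence of oliguria <500 mL/24 hr; increased serum creatinine (>30% from preoperative level".

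**Text extraction.** A fault in reading the PDF is unlikely. Inequality signs read sensibly elsewhere (the age criterion in section 4.2, the daily dose limit in section 9.1, the table in section 16.2), and here two opposite signs would both have had to flip in one sentence.

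**Logic.** Write C for cardiac index and S for stroke volume variation in percent. The limits 2.5 and 15 come from section 6. The four value pairs are assumed, chosen to cover each combination of sides.

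- Literal rule: fluid if C > 2.5 or S < 15.
- Correction A, either target missed: fluid if C < 2.5 or S > 15.
- Correction B, both targets missed: fluid if C < 2.5 and S > 15.
- Correction D, variation alone: fluid if S > 15.
- Correction E, index alone: fluid if C < 2.5.

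| C / S | Literal | A | B | D | E |
|---|---|---|---|---|---|
| 3.0 / 8% | yes | no | no | no | no |
| 3.0 / 20% | yes | yes | no | yes | no |
| 1.8 / 8% | yes | yes | no | no | yes |
| 1.8 / 20% | no | yes | yes | yes | yes |
| Pairs reversed against literal | – | 2 | 4 | 3 | 3 |

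The first and last rows are the clear-cut cases: good flow with low variation, and poor flow with high variation. The literal rule gives the opposite action to all four corrections in both. The two middle rows depend on which rule was meant. Corrections A and B are the readings the text can support, since it names both measures and joins them with 'or'. D and E are included only to show that the clear-cut result does not depend on that choice.

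**The case against.** The strongest reply is that the meaning can be recovered on the spot. Goal-directed therapy and a pressure goal come immediately before, the two values follow in the same form, and 'cut-off' can be read as a boundary whose crossing prompts fluid. A specialist is unlikely to give fluid because a patient's values are good. Section 6 also refers to a standardized anesthesia protocol that is not in the document, so the practical risk depends partly on what that says. The rule applies only if needed, in both arms, and the allocation list is "not accessible by participating observers or other personnel in the operating rooms, wards or by the attending surgeon, anesthesiologist or oncologist". The morbidity table in section 16.2 is a published instrument, so it is weak evidence of how the authors write their own thresholds.

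Most of this stands, and it settles how much the error matters. It does not make the sentence right. The text never calls the values targets; it calls them the cut-off for instability. The charitable reading also leaves 'or' between two targets, so a woman who misses only one of them is treated under correction A and not under correction B. The count of 2 to 4 reversed pairs reflects the correction chosen and is not an effect size. What is solid is that the two clear-cut cases are reversed.

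**Conclusion.** The sentence is wrong as written. Under the literal rule both clear-cut illustrative pairs (3.0 with 8%, and 1.8 with 20%) receive the opposite of the appropriate action, whichever correction is adopted. This rests on the ordinary meaning of the two measures and on assumed value pairs. The protocol does not state how many women would be managed under the rule, and no site is shown to act on the literal text.

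The consequence for the trial is small. The care is common to both blinded arms, low pressure has its own goal and vasopressor rule, and neither the definition of the primary endpoint (section 2.4.1) nor its analysis (section 8.3) uses these values. The sample size in section 8.4 (182, target 220), the power and the primary comparison are unaffected. It is a low-priority correction that favors patient safety.

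**What to change.** Correct the direction in one of two ways, keeping the limits 2.5 and 15%:

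- Reverse both signs, so that an index below 2.5 or a variation above 15% defines instability and prompts fluid.
- Relabel the values as targets to be maintained (index above 2.5, variation below 15%) and state that fluid is given when either is missed.

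Apart from values exactly at a limit, these two forms prescribe the same action. If the targets are stated without the second part, it stays open whether one missed target is enough. The sponsor's anesthesia leads can settle that in the same edit and check that the standardized anesthesia protocol used at the sites has the direction right. They may also wish to state what to do when index and variation are both low, but that goes beyond the error itself.

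The cost is one sentence in the next amendment, with no extra data, procedures or patients.

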### 4.3 Exclusion criteria

- Contraindication to epidural anesthesia
- Allergy to any component drugs used during epidural or intraperitoneal anesthesia (Ropivacaine, Sufentanil)
- Uncontrolled renal, liver, heart failure or ischemic heart disease
- Speech, language or cognitive difficulties
- Women in whom cytoreductive surgery is not attempted at time of upfront laparotomy due to extent of disease

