### 4.4 Randomization and registration

After verification of eligibility and signed informed written consent, women will be randomised at the morning of surgery to receive either Ropivacaine or saline by equal allocation, 1:1. The randomisation procedure will be pre-stratified for participating centre (permuted block design).

The Clinical Trials Unit at Centre for Clinical Cancer Studies Theme Cancer, Karolinska University Hospital, Stockholm, Sweden will perform the randomization centrally. All inclusion criteria and no exclusion criteria must be met. Inclusion and exclusion criteria are entered into the randomization/registration application, which is a web-based instrument (ALEA). Username and password are required to log in; each investigator authorized to register patients has a personal login user name and password. If all criteria are met, patients are registered, and the allocated patient study number is recorded in the patients' medical file. After randomization, confirmation e-mail will be sent out to the investigator, research nurse and principal investigator. Randomization will be performed by unblinded dedicated nurses not involved in the study in any other aspect. Each participating center

allocates one dedicated nurse (and one back-up nurse) who will be authorized to enter the web-based randomization system. After randomization a unique study number will be generated for each participant. The code list will be retained in a locked area only accessible to the unblinded nurse (-s).

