### 8.3 Data analyses

The primary endpoint, time to start of adjuvant chemotherapy will be analyzed using a linear regression model including the variable treatment. Results will be presented as the mean difference in days together with 95% confidence intervals and a Wald-test p-value. The significance level in the main analysis is set to 5%. Regression models including different clinical factors will also be estimated to take potential confounding into account. All analyses of primary and secondary outcome will be performed according to the intention-to-treat principle but may also be presented as per-protocol. For safety data, patients will be analyzed according to per-protocol approach.

Differences in complications, morbidity and in cardiac and renal impairment will be tested using Chi-square tests of independence. For dichotomous outcomes result will also be presented as differences in proportions together with 95% confidence intervals. Overall survival time will be calculated from the date of randomization to the date of death. For patients still alive, survival time will be calculated from the date of randomization to the date of last visit. Results from the survival analysis will be graphically presented as Kaplan-Meier curves. Proportional hazards regression models will be used to estimate the effect of the intervention on time to death. Results will be presented as hazard ratios 95% confidence intervals and Wald test p-values.

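### Women closed without resection are excluded after randomisation, and others can be sent to routine follow-up only: the analysis called intention-to-treat is a modified one and is open to informative missing data

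*Protocol*

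**What the plan says.** Section 4.4 of the protocol places allocation before the operation: "women will be randomised at the morning of surgery to receive either Ropivacaine or saline by equal allocation, 1:1". It sets an eligibility condition at that moment: "All inclusion criteria and no exclusion criteria must be met". Yet the exclusion list in section 4.3 contains "Women in whom cytoreductive surgery is not attempted at time of upfront laparotomy due to extent of disease". Section 6 states the consequence: if "the abdomen is closed without any resection of tumor, the participant is excluded from the IPLA-OVCA trial".

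Section 5.1 fixes when the first study dose is given: "After opening the peritoneal cavity and before any surgical dissection, 40 ml of the Ropivacaine will be rinsed in all quadrants". Section 5.3 says the same for both arms.

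Section 4.6 lets the investigator or sponsor end the study for a woman. The examples given are unacceptable adverse events or reactions, or "because the subject does not follow procedures in the study protocol". After discontinuation she is followed by the clinic's routine. The section does not say whether her trial outcomes are still collected.

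Section 8.3 states: "All analyses of primary and secondary outcome will be performed according to the intention-to-treat principle". A per-protocol presentation is optional for these outcomes. Safety data are to be analysed by a per-protocol approach.

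**The concern.** Intention-to-treat normally means that every randomised woman is analysed in her allocated arm. Two rules in the protocol pull against that.

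The first is the exclusion at laparotomy. It removes randomised women from the trial itself, and not merely from study drug or from one analysis. Two things are at stake. The primary population is narrower than its label says. And women who have had study drug may drop out of the safety and survival data.

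The second is termination under section 4.6. Its grounds, adverse events and non-adherence, can depend on the treatment given and on how recovery is going. Sections 1.1.1 and 13 name complicated recovery as a cause of delayed chemotherapy, and that delay is the primary outcome. If outcomes stop being collected for these women, the missing values may be related to the endpoint and to the arm.

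**Working it through.** **1. Order of events, with the section for each step**

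| Step | Section | Consequence |
|---|---|---|
| Eligibility verified, no exclusion criterion met | 4.4 | Must be complete before allocation |
| Randomisation, morning of surgery | 4.4, 6.1 | The woman belongs to an arm |
| Peritoneum opened, Dose 1 given before dissection | 5.1, 5.3 | Exposure begins |
| Cytoreduction attempted or not | 4.3, 6 | The last exclusion criterion becomes knowable |
| If closed without resection, excluded from the trial | 6 | Removed after randomisation |
| Analysis by intention-to-treat | 8.3 | Claimed for all primary and secondary outcomes |

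The protocol does not fix the order of Dose 1 and the operability judgement. The table shows a possible order, not a stated one. In either order the exclusion comes after randomisation, so the check required by section 4.4 cannot be complete when it is made. The set left for the primary analysis is a modified intention-to-treat set, which the protocol does not name.

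**2. Possible exposure of an excluded woman**

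Dose 1 is 40 ml of 2 mg/ml (sections 5.1 and 5.3): 40 × 2 = 80 mg in the active arm, if it was given before the decision to close.

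**3. What section 4.6 does and does not remove**

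The section ends participation. It does not say that data leave the analysis. Section 6.1 has the chemotherapy start recorded at about 6 months and reads vital status from the medical records at 3 and 5 years. The data therefore probably exist. What is missing is an instruction to collect and use them after termination.

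**4. The sample size, reproduced first**

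Inputs from section 8.4: difference 5 days, SD 12, two-sided 5%, power 80%.

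n per arm = 2 × (1.96 + 0.8416)² × 12² / 5² = 2 × 7.849 × 5.76 = 90.4, rounded up to 91. The total is 182, as stated.

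The target of 220 agrees with 182 × 1.2 = 218.4, rounded up to 219. It does not agree with 182 / 0.8 = 227.5, rounded up to 228. The margin is 220 − 182 = 38 women, or 38/220 = 17.3%.

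**5. Effect of the laparotomy exclusion on numbers**

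The documents give no no-resection rate, so 5% to 15% is assumed. Power = Φ(5 / (12 × √(2/m)) − 1.96), with m women per arm.

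| Assumed no-resection rate | Women removed | Remaining of 220 | Power, no other loss |
|---|---|---|---|
| 5% | 11 | 209 | 85.4% |
| 10% | 22 | 198 | 83.4% |
| 15% | 33 | 187 | 81.3% |

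All three stay above 182. If the exclusions came on top of the full 20% drop-out, the numbers would be 220 × 0.95 × 0.8 = 167 down to 220 × 0.85 × 0.8 = 150. Section 8.4 does not say which reading is meant.

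**6. Would analysing every randomised woman give more power?**

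Assume all outcomes are obtained, the SD is unchanged and there is no effect in unresected women. The average effect is then 5 × (1 − rate), with 110 per arm:

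- 5%: 4.75 days, power 83.5%
- 10%: 4.50 days, power 79.4%
- 15%: 4.25 days, power 74.8%

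This is below the table above at every rate. Power is therefore no argument against a primary set restricted to attempted cytoreduction.

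**The case against.** The strongest defence of the laparotomy rule is that it is announced in advance (synopsis, sections 4.3 and 6), depends on disease extent, and is applied by a surgeon who has no access to the allocation list (section 4.5). Section 8.1 defines the endpoint as time to chemotherapy after cytoreductive surgery, so the rule matches the population of interest. All of this stands. Bias between arms from this rule should be small, and a primary set of women with attempted cytoreduction is reasonable.

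A reader might infer that every excluded woman has been dosed and is then lost to safety and survival follow-up. The documents do not say so. Section 12.1 defines an adverse event for any subject given study drug. Section 12.1.2 runs serious adverse event reporting to day 33, section 12.5 follows all adverse events, and section 15.1 requires a case report form for every consented woman who has had any screening procedure. None of these exempts an excluded woman. But none says that it overrides section 6 either. Section 12.4.2 allows follow-up of a serious event to stop when participation is completed, and section 4.7 has no category for women excluded at laparotomy. The data are at risk, not certainly lost.

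On section 4.6, it is fair to say that handling of missing data is commonly left to the analysis plan. Also, section 12.4.1 states that postoperative complications are not analysed as adverse events, so the women terminated need not be those with complications. This limits how strongly the bias can be asserted.

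Finally, naming an analysis set is ordinary analysis-plan content. That answers the label but not the rest: an analysis plan cannot recover data that the protocol's own rules caused not to be collected.

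**Conclusion.** Sections 4.3, 4.4, 4.6, 6 and 8.3 conflict and must be reconciled. The laparotomy exclusion makes the primary analysis a modified, not a full, intention-to-treat analysis. It also leaves follow-up uncertain for women who may have received up to 80 mg of study drug. Section 4.6 adds a risk of informative missing data.

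It would be too strong to conclude that intention-to-treat cannot be done. Section 4.6 does not delete anyone's data, and the key outcomes can be read from the record. The size of any bias from section 4.6 cannot be given: the documents state neither how many women would be terminated nor how their chemotherapy dates would differ.

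A reader might also infer that the exclusions alone leave the trial underpowered. At the assumed 5% to 15% they do not: 209 to 187 women remain against 182 required. A shortfall needs total losses above 17.3%. The proposed change would not restore power, because unresected women stay outside the primary set. Its value lies in correct labelling and in complete safety, survival and endpoint data.

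**What to change.** 1. **Sections 4.3, 6 and 8.3.** Name the primary set as all randomised women in whom cytoreduction was attempted, with that judgement made blind to arm. Report the number removed in each arm. State that randomised women without resection, especially those who received any study drug, stay in serious adverse event reporting to day 33 and in survival follow-up. Reword section 4.4 so that the laparotomy criterion is not presented as checkable at randomisation.
2. **Section 4.6.** State that ending study treatment, or non-adherence, does not end data collection. Chemotherapy start date, 30-day complications, serious adverse events and vital status are still taken from the record and analysed as randomised, unless the woman withdraws consent to this.
3. **Section 8.4.** Say whether laparotomy exclusions count within the 20% drop-out.

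The cost is amendment wording and a small amount of record review. The timing of randomisation need not change. Moving it into the operation would disturb the preparation of blinded syringes before surgery (section 5.3), and the changes above do not depend on it.
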